### **11.3.2. Descriptive statistical methods**

Categorical variables will be described in terms of numbers, percentages and possibly 95% confidence intervals according to the exact binomial distribution.

Quantitative variables will be described in terms of number, mean, standard deviation, possibly 95% confidence interval of the mean, median, range and interquartile range.

### **11.3.3. Participants included in the analysis**

Only participants who meet at least one of the following conditions may be excluded from the analysis:

- Participants who never followed the research procedure (provided they were not aware of the group to which they were randomized),
- Participants wrongly included for unsigned consent,
- Participants who withdrew their consent.

This exclusion decision will be taken by the Scientific Council of the trial after documentation of the observation by the Methodology and Data Management Center (EUCLID), without regard to the strategy group and the participant's evolution after inclusion.

Apart from these exclusions, all participants who died, were lost to follow-up, or dropped out of the research will be included in the analysis.

### **11.3.4. Characteristics of the participants**

Participants will be described according to the following variables:

- Compliance with eligibility criteria;
- Epidemiological characteristics (demographics, disease history, and characteristics at inclusion);
- Clinical characteristics;
- Biological characteristics.

A description of the protocol violations and the participants distributed according to these violations will be provided .

A description of causes of death and dropout will be made and participants who died, were lost to follow-up, or dropped out of the research will be described and compared to other participants.

Epidemiological characteristics at inclusion of meditating seniors will be compared to non-expert seniors.

### **11.3.5. Analysis of the main criteria**

The comparison between the meditation group and the foreign language learning group will look at the difference in 1) volume and 2) perfusion of the anterior cingulate cortex 18 months after the start of the intervention compared to the value at inclusion.

The comparison between the meditation group and the no-intervention group will look at the difference in 1) insula volume and 2) insula perfusion 18 months after the start of the intervention compared to the value at baseline.

The main criteria will be compared between groups by Student's t test or Wilcoxon test if the hypothesis of normality of the criteria is not verified.

An analysis of the effect of the level of exposure to meditation (number of hours of practice, number of sessions, etc.) will be performed by including all participants.

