## 2. OBJECTIVES

This research aims to **determine the effects of an 18-month meditation practice on imaging, biological, and behavioural markers** particularly associated with aging and AD and **to better understand the cognitive and emotional mechanisms** underlying these effects. All the objectives and corresponding analyses are detailed below.

We hypothesize that an 18-month meditation intervention will result in an increase in volume and/or perfusion of the anterior cingulate cortex. This intervention will be compared to a passive control (participants receiving no intervention in the trial). We also hypothesize that an 18-month meditation intervention will result in increased volume and/or perfusion of the insula compared to a foreign language

learning intervention, designed to have a similar structure to the meditation intervention. The non-specific effect of meditation on the anterior cingulate cortex will be estimated by comparing it to the passive control group. The specific effect of meditation on the insula will be estimated by comparing it to the foreign language learning group.

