## **2.1. Main objectives**

The **main objectives** of the trial are:

- To estimate the effect of an 18-month meditation intervention in non-meditating senior participants on volume and perfusion of the anterior cingulate cortex compared to a passive control (**OBJECTIVE 1**);
- To estimate the effect of an 18-month meditation intervention in non-meditating senior participants on the volume and perfusion of the insula compared to an 18-month foreign language learning intervention (**OBJECTIVE 1bis**).

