### 5.1. Main evaluation criteria

- For the comparison between meditation group and passive control group (OBJECTIVE 1):
  - Volume difference in the anterior cingulate cortex measured on T1-weighted MRI at inclusion and at 18 months;
  - Perfusion difference in the anterior cingulate cortex measured by PET (early frames of the radiopharmaceutical Amyvid®) at inclusion and at 18 months.
- For the comparison between meditation group and foreign language learning group (OBJECTIVE 1bis):
  - Volume difference in the insula measured on T1-weighted MRI at inclusion and at 18 months;
  - Perfusion difference in the insula measured by PET (early frames of the radiopharmaceutical Amyvid®) at inclusion and at 18 months .

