## 1.7 Outcomes

### 1.7.1 Primary outcomes

For the comparison between meditation intervention and no intervention (**OBJECTIVE 1**):

- Change in anterior cingulate cortex volume (T1-weighted MRI) from baseline to 18 months;
- Change in anterior cingulate cortex perfusion (early PET-Amyvid® scan) from baseline to 18 months).

For the comparison between meditation intervention and language learning intervention (**OBJECTIVE 1BIS**):

- Change in insula volume (T1-weighted MRI) from baseline to 18 months;
- Change in insula perfusion (early PET-Amyvid® scan) from baseline to 18 months).

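### Protocol 11.3.5 swaps the comparators for all four primary tests, contradicting the objectives, endpoints, sample size and both SAPs

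*Combined protocol and SAP*

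**What the plan says.** Protocol 11.3.5 gives the primary analysis in two sentences. The first, on meditation versus English, reads in part: "foreign language learning group will look at the difference in 1) volume and 2) perfusion of the anterior cingulate cortex 18 months after". In the second, on meditation versus no intervention, we find: "The comparison between the meditation group and the no-intervention group will look at the difference in 1) insula volume and 2) insula perfusion", again at 18 months against baseline.

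Protocol 2.1 sets the opposite pairing. Objective 1 concerns the effect of meditation "on volume and perfusion of the anterior cingulate cortex compared to a passive control". Objective 1bis concerns its effect "on the volume and perfusion of the insula compared to an 18-month foreign language learning intervention".

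Protocol section 2 gives the reason for each half: "The non-specific effect of meditation on the anterior cingulate cortex will be estimated by comparing it to the passive control group", and "The specific effect of meditation on the insula will be estimated by comparing it to the foreign language learning group".

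Protocol 5.1 and 11.2 repeat the pairing in 2.1. So does section 1.7.1 of the primary SAP, which lists change in cingulate volume and perfusion under the heading "For the comparison between meditation intervention and no intervention" and the two insula outcomes under meditation versus language learning.

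**The concern.** Section 11.3.5 is the protocol's own rule for the confirmatory tests, and both of its sentences disagree with the objectives they are meant to serve.

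The pairing carries the scientific claim. The insula is set against an active control so that an effect can be read as specific to meditation. The cingulate is set against no intervention to capture a non-specific effect. Under 11.3.5 the insula would be tested without an active control, and neither stated inference could be drawn.

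Nothing in the data would expose the mistake. Protocol 6.2 (Table 3) schedules the inclusion and 18-month imaging in all three arms, and 10.4 has volume and perfusion of both regions entered in the eCRF. The swapped contrasts could be computed without any technical warning.

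**Working it through.** The question is mainly textual, so the pairings are set side by side first.

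| 18-month change in | Meditation compared with: objectives, endpoints, sample size, both SAPs | Meditation compared with: protocol 11.3.5 |
|---|---|---|
| Cingulate volume | No intervention | English |
| Cingulate perfusion | No intervention | English |
| Insula volume | English | No intervention |
| Insula perfusion | English | No intervention |

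Agreement is 0 of 4.

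The middle column is stated in these places:
- Protocol synopsis: main objectives, primary endpoint, study size.
- Protocol body: section 2 (hypotheses), 2.1, 5.1, 11.2.
- Primary SAP: 1.2.1, the sample-size text that follows 1.6.2, and 1.7.1.
- Secondary SAP: main objectives, sample size, primary outcomes.

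That is 3 + 4 + 3 + 3 = 13 places. (The sample-size texts of the two SAPs say metabolism where the outcomes say perfusion; the pairing of regions and arms is the same.) The right-hand column is stated only in 11.3.5.

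The primary SAP's analysis paragraph, 3.6.1, does not name the pairs. It refers to the four comparisons, so the pairing has to be read from 1.7.1 of the same document, where it is the intended one.

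Next, whether the swap touches the design figures.

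**Sample size.** Inputs from protocol 11.2: standardised effect 0.75, power 80%, two-sided alpha 1.25%, equal arms.
- Normal approximation: n per group = 2 x (z for 1 - 0.0125/2, plus z for 0.80)² / 0.75² = 2 x (2.498 + 0.842)² / 0.5625 = 39.7, so 40.
- Solution based on the t distribution: 41.24, so 42. This reproduces the stated 42 per group and 126 in total.
- Power by the t-based calculation: 80.9% with 42 per group and 88.3% with 50 per group.

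Every contrast, in either pairing, uses the same effect size, alpha and arm sizes. Correcting the pairing therefore changes none of these figures.

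**Type I error.** Primary SAP 2.1.3 gives each of four tests 1.25%: 4 x 1.25% = 5%. This is also unchanged.

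**Status of the swapped contrasts.** Protocol Objective 2 (2.2.1) compares the two interventions with each other and with passive control on imaging measures. Protocol 5.2 lists voxel-wise grey matter volume and perfusion, and 11.3.6 allows region-of-interest analyses. The four contrasts in 11.3.5 therefore exist in the plan, but only as secondary comparisons.

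**The case against.** The strongest reply is that this is a transposition in a summary chapter. Protocol 11.3 says the SAP is a separate, complete document and that the chapter gives only its main elements. The EUCLID statistician analyses the main objectives, and the primary SAP has the right pairing in its objectives, sample size and outcomes. A statistician who follows the SAP tests Objectives 1 and 1bis. That stands, and it limits the harm to the case where 11.3.5 is followed or later cited.

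It does not remove the contradiction. The documents contain no rule saying which text governs. The primary SAP declares itself based on protocol v5.0 of 24/04/2017, while the protocol's version history runs to v12.0 of 07/01/2022.

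A reader might infer from those dates that the swapped pairing is the more recent intention. The documents do not support this. Version 12 itself states the intended pairing in its synopsis and in sections 2, 2.1, 5.1 and 11.2, and the secondary SAP, based on v9.0 and v10.0, repeats it. The available documents do not show when the swap entered the text.

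A reader might also infer that the trial never set the contrasts in 11.3.5. That is true of the primary hypotheses only, since Objective 2 covers them as secondary.

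**Conclusion.** Section 11.3.5 is wrong as written. It misassigns the comparator in all four primary tests and contradicts the rest of the protocol and both SAPs. If followed, it would test none of the four contrasts that make up Objectives 1 and 1bis and would raise four secondary contrasts to primary status.

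The conclusion rests on reading the 13 concordant statements, with the rationale in protocol section 2, as the intended plan. It does not imply that the analysis in the primary SAP is wrong, nor that sample size, power or alpha needs to change.

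A reader might go further and infer an inflated family-wise error from having two sets of primary tests. If both sets were run at 1.25%, the Bonferroni bound would be 8 x 1.25% = 10% (1 - 0.9875^8 = 9.6% if the tests were independent). No section plans this, and protocol 11.2 and primary SAP 2.1.3 limit the family to four comparisons, so the figure is hypothetical and is not part of the finding.

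**What to change.** Rewrite the first two sentences of 11.3.5 so that:
- meditation versus passive control is tested on 18-month change in cingulate volume and cingulate perfusion;
- meditation versus English is tested on 18-month change in insula volume and insula perfusion.

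Add that the four swapped contrasts (meditation versus English on the two cingulate outcomes, meditation versus no intervention on the two insula outcomes) are secondary.

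Record the change as correcting an error against protocol 2.1, 5.1 and 11.2 and the primary SAP. This matters because v12.0 is dated after 31 December 2020, the date after which protocol 10.5 plans to transfer the frozen database running through the 18-month visit. Without that record, the correction could be mistaken for a choice made after seeing data.

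The cost is one paragraph of protocol text. Data collection, design, sample size and alpha do not change.

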In addition, participants will be asked to fill in a "diary" throughout the intervention to indicate the exercises performed and to assess whether they are difficult or pleasant (see also 5.3). Indeed, in order to quantify the daily practice of the participants throughout the trial and to allow us to analyze in a more detailed way the impact of the inter-individual differences of daily practice on the primary and secondary variables of the trial on the one hand, and to allow the participants to use the pedagogical material (audios) used in the interventions on the other hand, an Ipad tablet is lent to the participants during their entire participation in the trial. The functionalities of the Ipad which are not required for the trial have been deactivated (Internet...). The latter contains an application for an Ipad 2 tablet, containing a questionnaire of 6 daily questions and developed internally by [name]'s team at the Centre de Recherches en Neurosciences de Lyon, Inserm. The 6 questions intended for the subjects of the English and meditation groups are composed of 4 multiple choice questions and 2 open questions. The first question concerns the well-being of the person (the choice of answers is presented in the form of a table in which the rows represent different intensities (very big, big, small, very small) and the columns different weather images (sun, sun and small cloud, sun and big cloud, cloud, rain, flash cloud, double flash). The second question asks about formal practice time for the day (0 min, less than 15 min, between 15 and 30 min, between 30 and 45 min, between 45 and 60 min, between 60 and 90 min, between 90 and 120 min, over 120 min). Formal practice is defined as practice related to the instructions, exercises, or materials (books and applications) of the course for the English intervention. For the meditation group, formal practice is defined as practicing meditation exclusively without doing another activity at the same time. The third question asks about the duration of their informal practice (0 min, less than 15 min, between 15 and 30 min, between 30 and 45 min, between 45 and 60 min, between 60 and 90 min, between 90 and 120 min, more than 120 min). Finally, the fourth question asks about motivation to practice during the day (very low, low, medium, high, very high). The fifth question asks about the geographic area where the subject is located during the day (free text). The last question gives subjects the opportunity to leave comments on the intervention in general.

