## **10.4. Data circuit before computer entry**

Regarding the consistency check of the collected data, they are retrieved once a month for each participant in the English group and the meditation group. On this occasion, we can verify that the tablet is working as intended. In addition, we record the participants' data via the Kallysta case and the Dapi software installed on a MacBook computer that is not connected to the internet or any intranet and is password protected. We then check that the participants fill in the questionnaire according to our expectations (once a day). This is the first method that allows us to know that the use of the tablets by the participants is consistent with our expectations. The second method we use goes into a little more detail about the data recorded. In particular, we track practice time by verifying that, on the day of the weekly course, participation is around 2 hours on average for the participants. We can then confirm that participants are filling out their tablets as we explained to them. If this is not the case for a participant, we can re-explain the instructions for correctly filling out the questionnaire on the tablet.

As for the maintenance of the equipment, tablets, computers and briefcases, this is carried out by the computer specialists of the center where the equipment is located: the computer specialists of the Carré international for the equipment attached to the English learning intervention and the Cyceron center for the equipment attached to the meditation intervention. In both cases, the equipment is stored in locked cabinets, in locked rooms. In addition, to enter these buildings, it is necessary to use a biometric code to gain access.

Concerning the traceability of the data, they are recovered by wire from the tablet and without the need for an internet network. The saved file has the date of recording and data collection.

These data files collected via the tablets will then be decrypted and formatted at Cyceron by a member of [name]'s team and transferred to an Excel spreadsheet. This Excel table will then be sent in a secure way to the data management team who will keep this file for later availability with the database from the eCRF, the anonymization code being the element that allows to match the collected data to the right participant.

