### 2.3 Comparative analysis

Qualitative variables will be compared between the groups with the  $\chi^2$  test or the corrected  $\chi^2$  or non-parametric Fisher's exact test, according to the values of expected frequency under the independence assumption. A logistic or polytomic model will be used to consider adjustments if necessary. The assumption of log-linearity of the association will be systematically checked.

Quantitative variables will be compared between 2 groups of intervention by Student t test if the conditions of validity are respected (normal distribution, homogeneous variances). If the variances are unequal between the 2 groups, a t-test for unequal variances will be used, if the distribution is not normal, a non-parametric Wilcoxon test will be used.

A linear regression model will be used to adjust on variables if necessary. The assumption of linearity of the association will be systematically checked. The other assumptions of the model (normality and homoscedasticity of residuals) will be studied. A transformation of the quantitative variable may be considered if necessary.

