### 3.4.2 At the end of the trial

- Death
- Compliance
  - Total number of classes attended
  - Total number of reported practice sessions
  - Total number of minutes of formal practice
  - Total number of minutes of informal practice
- Adverse events
  - Severity
  - Relationship to the study intervention or radiopharmaceutical drugs

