## STATISTICAL ANALYSIS PLAN

$\Delta = (\text{measure at 18 months} - \text{measure at inclusion})$

The four comparisons will be first conducted according to the intent to treat principle with “missing = failure” strategy (see §2.3 for comparative statistical tests) for handling missing data on primary endpoints. A failure is defined as the minimum change between baseline and 18 months observed in the whole population study. This first analysis will be the main result of the study.

This first analysis will be complemented with a sensitivity analysis to check the robustness of the main analysis to missing data. The maximum bias strategy for missing data will be performed. Missing data will be replaced by a failure of the strategy in one group and by a success of the strategy in the other, and vice versa. The success is defined as the maximum change between baseline and 18 months observed in the whole population study. The failure is defined as the minimum change between baseline and 18 months observed in the whole population study.

We will be able to conclude that the first analysis is robust if all sensitivity analyses have a similar conclusion.

The main and sensitivity comparative analyses will be performed with adjustment on baseline prognostic factors (age, education, gender, MMSE) (see §2.3 for statistical models).

A per-protocol analysis will be performed, using the strategy defined in §2.1.1.

An analysis of the effect of the exposure to meditation (number of hours of practice, number of sessions...) will be performed using the strategy described in §2.3.

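### The meditation exposure analysis pools all participants without an arm term, so its slope largely restates the between-arm difference and cannot show whether more practice gives more effect

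*Combined protocol and SAP*

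**What the plan says.** Protocol 11.3.5 ends with an analysis of the level of exposure to meditation, measured by hours, sessions and similar: "number of sessions, etc.) will be performed by including all participants". The primary-objectives SAP keeps it in section 3.6.1 and points to section 2.3 for the method: "An analysis of the effect of the exposure to meditation (number of hours of practice, number of sessions...) will be performed using the strategy described".

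Section 2.3 deals with comparisons between groups. Its only regression provision for quantitative outcomes is this: "A linear regression model will be used to adjust on variables if necessary". No exposure–response model is written down. The covariates that 3.6.1 names for the main and sensitivity comparisons are "adjustment on baseline prognostic factors (age, education, gender, MMSE"; study arm is not listed.

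Protocol 6.8 asks participants to stay away from the activities of the other arms and gives the passive group no intervention. It also gives the purpose of the practice diary: to study how differences between individuals in daily practice relate to the primary and secondary variables. Only the English and meditation groups keep the diary, and in the English group formal practice means work on the English course. Time is ticked in bands, the highest being "between 60 and 90 min, between 90 and 120 min, over 120 min", so the last one is open. SAP 3.4.2 lists as a compliance item "Total number of minutes of formal practice", next to counts of classes attended and of reported practice sessions.

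**The concern.** A dose–response slope is informative when people with different doses are otherwise comparable. Here two of the three randomised arms have dose zero for everybody, and the third holds all the positive doses. A regression of change on hours across all participants then has two sources of information: the gap between the zero-dose arms and the meditation arm, and the spread of hours inside the meditation arm. The first dominates. If meditation shifts the outcome by the same amount for everyone who attends, however much they practise, the pooled slope is still positive.

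At stake is the reading of a positive trial. A significant exposure slope beside a significant arm difference looks like independent support from a dose–response relation, when it may be the same difference counted again. It would also leave unanswered the question the protocol sets the diary to answer.

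**Working it through.** **Inputs.** Arm size 50 and 1:1:1 allocation (protocol 3.2). Planned effect d = 0.75, power 80%, two-sided alpha 1.25% (protocol 11.2). Zero meditation exposure outside the meditation arm (protocol 6.8). The documents give no spread of practice hours, so the coefficient of variation (CV) is an assumption, taken as 0.3, 0.5 and 0.8.

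**The plan's own figure.** The documents state no operating characteristic for the exposure analysis. The sample size behind d = 0.75 does reproduce: alpha is 0.05/4 = 0.0125, and the exact noncentral t gives power 79.7% at 41 and 80.9% at 42 per group, against the stated 42.

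**What the pooled slope estimates.** Scale dose to mean 1 in the meditation arm and 0 elsewhere. Let the outcome have SD 1, a shift of d in the meditation arm, the same mean in the other two arms, and no dependence on dose within the meditation arm. One third of participants are in that arm, so:

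- Cov(dose, arm) = 1/3 − 1/9 = 2/9
- Var(dose) = (1 + CV²)/3 − 1/9 = (2 + 3CV²)/9
- pooled slope = d × 2/(2 + 3CV²)

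With d = 0.75 this gives 0.75 × 2/2.27 = 0.66, 0.75 × 2/2.75 = 0.55 and 0.75 × 2/3.92 = 0.38 SD per mean dose for CV 0.3, 0.5 and 0.8. The true within-arm slope is 0 in each case. The simulated mean slopes are 0.66, 0.55 and 0.40, and the simulated correlations between dose and arm are 0.94, 0.86 and 0.72.

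**How often it is significant.** 4,000 simulated trials per setting, 50 per arm, gamma-distributed dose, percentage with p<0.05 for the pooled slope:

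| Arm effect d | CV 0.3 | CV 0.5 | CV 0.8 |
|---|---|---|---|
| 0 | 4.7 | 5.2 | 4.6 |
| 0.25 | 26.8 | 23.1 | 19.4 |
| 0.5 | 76.5 | 68.8 | 53.8 |
| 0.75 | 98.0 | 95.8 | 85.7 |

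The Monte Carlo standard error is at most √(0.25/4000) = 0.8 percentage points. At 42 per arm and d = 0.75 the range is 80% to 95%. If the 1.25% level were used instead, d = 0.75 with 50 per arm gives 93%, 87% and 69%. Pooling only the meditation arm and one comparator does not cure the problem: 92% to 68% at d = 0.75 over the same CVs, at the 5% level.

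**With the fix.** Fitting the slope in the meditation arm only, or in all arms with a meditation-arm indicator, gives a mean slope of about 0 and p<0.05 in about 5% of trials in every setting.

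**Diary bands.** Eighteen months is 18 × 30.4375 = 547.9 days. Someone who ticks the 15–30 minute band every day has a total between 547.9 × 15/60 = 137 hours and 547.9 × 30/60 = 274 hours. These are outer limits. If minutes varied independently and evenly within the band, the total would be close to 547.9 × 22.5/60 = 205 hours.

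**The case against.** The best defence is that including all participants means regardless of adherence. Protocol 11.3.1 has just described a sensitivity analysis limited to people who attended at least 20% of sessions, and 11.3.5 may simply be lifting that limit within the meditation arm. SAP 3.6.1 drops the phrase, the diary's stated purpose points to variation within an arm, and the secondary-objectives SAP refers to exposure to meditation and to English, working within the two intervention groups for Objective 2bis. This reading is possible. But neither 11.3.5 nor SAP 3.6.1 says it, and it leads to the same correction: write the population down.

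It is also fair that the analysis is supportive. SAP 3.6.1 makes the intention-to-treat comparison the main result, and nothing confirmatory rests on the slope.

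Several stronger readings should be resisted:

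- A reader might infer that a dose effect will appear whenever the arms differ. At d = 0.25 it appears in roughly a fifth to a quarter of trials.
- A reader might infer inflated type I error. With no arm difference the rate stays near 5%.
- A reader might infer that practice minutes cannot be derived from the diary. Only exact totals are out of reach. Bounds and approximations are available, and class and session counts do not depend on the bands.
- Protocol 10.4 checks that "on the day of the weekly course, participation is around 2 hours on average", so class time does enter the diary, and a reader might infer that classes are counted twice. No section adds attended classes to diary time; SAP 3.4.2 lists them separately.

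**Conclusion.** The point holds. As written, the exposure analysis credits an arm effect to dose and cannot answer the protocol's question about differences in practice between individuals. At the planned effect size, a significant pooled slope is expected in about 86–98% of trials even if the amount of practice is irrelevant.

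Those figures rest on four assumptions: a model without an arm term, which is what the documents leave; a CV of hours between 0.3 and 0.8; equal means in the two zero-dose arms; and zero exposure taken from the design, since the passive arm keeps no diary and the English arm's diary records English work.

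The correction should be made, but the primary between-arm tests do not depend on it. The banded diary is a minor note: practice totals are approximate and the plan gives no rule for turning bands into minutes.

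**What to change.** In protocol 11.3.5 and SAP 3.6.1, state that exposure–response is estimated in the meditation arm only, including every meditation participant regardless of attendance. Alternatively, keep all arms, add a meditation-arm indicator and report the within-arm slope. In either case adjust for age, education, gender and MMSE, and label the result as a non-randomised comparison by adherence: restricting the population removes the arm artefact but not confounding by who chooses to practise.

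As a secondary clarification, describe diary time as approximate and use classes attended or number of practice sessions as an exposure measure that does not depend on the bands. Both counts are already listed in SAP 3.4.2.

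The change costs wording only; no new data are needed. The price is precision. With residual SD 1, the standard error of the within-arm slope is about 1/(CV × √50), that is 0.47, 0.28 and 0.18 SD per mean dose for CV 0.3, 0.5 and 0.8. For the pooled slope it is about 1/√(150 × (2 + 3CV²)/9), that is 0.16, 0.15 and 0.12. The pooled slope's smaller error comes largely from the arm contrast, which is not information about dose.
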